
### Data management

Paper data and documentation containing personal identifiers will be held in locked cabinets in locked offices in each implementation site. Data collected using pen and paper methods will be entered into an Excel spreadsheet independently by two members of the research team. Qualitative data from audio recorded (MPEG-1 Audio Layer 3; mp3) individual interviews will be anonymised and transcribed (Rich Text File) in the language of the interview. All electronic files will be encrypted, password-protected, and using a secure network.

### Data analyses

The primary outcomes of this pilot are the feasibility, acceptability, appropriateness, and fidelity of the Thriving Mamas programme and provider training. Recommendations for implementation-focused pilot studies suggest the use of descriptive statistics to inform a larger scale evaluation [40]. They are not designed to detect a treatment effect. Our data analysis plan is developed in line with these recommendations and informed by the CONSORT extension of randomised pilot and feasibility trials [41] and the Standards for Reporting Implementation Studies (STAaRI; [42]) guidelines.

#### Quantitative analysis

Descriptive statistics of implementation outcomes (FIM, AIM, IAM) will be calculated. These measures will be compared with different baseline characteristics (e.g. age) to develop further insight into influencing factors. Continuous outcomes (PHQ-9 and GAD-7) will be evaluated using linear regression models that adjust for clustering using a dummy variable (due to the small number of clusters), urban vs rural setting, and any obvious imbalances between treatment arms determined at baseline. Coefficients and associated 95% confidence intervals for these outcomes represent differences in means between intervention and control arms. Mean differences from baseline to the end of the intervention will be assessed for clinical outcomes (e.g. quality of life, social support, and parenting competency) in each arm. These will be discussed with local stakeholders to aid in determining clinical minimally important differences (MIDs) to inform the sample size for a full trial. The cost of training and intervention delivery will be tallied to provide a total cost of intervention delivery. Data on the costs to adolescents and friends/family members in taking part in the intervention will contribute to the assessment of the feasibility and sustainability of the intervention.

Patterns and the proportion of missing data will be investigated. If there are any marked differences in missing data between treatment arms, or if greater than 10% of the data are missing, multiple imputation using chained equations (MICE) models under the assumption that data are missing-at-random will be used for all the analyses described above. All analyses will be conducted in STATA v.17.

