### Participants and sampling method

The sample size for the pilot has been selected on the grounds of feasibility of recruitment and retention of participants in both study arms and was informed by local partners and stakeholders. This study aims to enrol 80 adolescent girls and 32 mentor mothers, with a loss to follow-up of 33% for both cadres of study participants. This will enable estimation of the loss of follow-up rate with a 95% CI of ± 17% for mentor mothers and ± 11% for adolescent girls [14, 15]. This, in turn, will provide us with essential information required to calculate the sample size for the main trial.

We also anticipate that our sample size will provide us with insight into whether the intervention is acceptable, appropriate, feasible, and delivered with high fidelity. If our findings suggest otherwise, this will indicate that further work is needed to adapt the intervention and selected implementation strategies, prior to implementation.

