#### Adolescent girls

Up to 40 adolescent girls will be recruited in each country (*n* = 80), through participating community services and health facilities. In Kenya, adolescents will be recruited from local dispensaries. In Mozambique, adolescents will be recruited from primary health centres. The following inclusion criteria will be used: (a) up to 28 weeks pregnant; and (b) aged 15–19 years. They will be excluded from the study if they are unable to provide informed consent or are unable to participate in the intervention, due to existing health conditions.

Adolescent girls who meet the study inclusion criteria will be given information about the study by health facility staff. Those interested in participating will be introduced to a member of the research team, who will provide them with an information sheet and consent form. Where an adolescent is aged 15–17 years, the research team also will discuss the information with their guardian during the same visit, if the guardian is in attendance. If the guardian is not present, a member of the research team will discuss the information sheet with the minor. If she indicates further interest in participating, we will explain that we also require guardian consent due to her age. Following introduction to their guardian, the study will be introduced using the information sheet and consent requested. In this situation, the minor will be required to provide their assent following guardian consent.

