### Randomisation

Allocation to the intervention or control group will be carried out by randomisation of health facilities (clusters). This will ensure the inclusion of an urban and peri-urban site in both the intervention and control groups (i.e. stratification). In both countries, clusters will be geographically separated to reduce the potential for contamination.

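### Facility dummies in the PHQ-9 and GAD-7 regressions are collinear with the facility-randomised arm, so the coefficient is not the between-arm difference the plan says it is

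*Protocol article*

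**What the plan says.** All references are to the protocol article.

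- **Randomisation:** "Allocation to the intervention or control group will be carried out by randomisation of health facilities (clusters" is the allocation rule. On the sites, it adds: "This will ensure the inclusion of an urban and peri-urban site in both the intervention and control groups (i.e. stratification".
- **Quantitative analysis:** the continuous outcomes, PHQ-9 and GAD-7, are to be analysed by "linear regression models that adjust for clustering using a dummy variable (due to the small number of clusters" being the stated reason. The same model also adjusts for "urban vs rural setting, and any obvious imbalances between treatment arms determined at baseline".
- **Quantitative analysis, next sentence:** "Coefficients and associated 95% confidence intervals for these outcomes represent differences in means between intervention and control arms".
- **Participants and sampling method:** "This study aims to enrol 80 adolescent girls and 32 mentor mothers, with a loss to follow-up of 33" per cent expected.

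The visible text does not give the number of facilities, and the pilot flow diagram is not shown. The data analyses section makes implementation outcomes primary. The description of measures for adolescent girls names depression as the study's primary outcome.

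**The concern.** Every girl at a facility is in the same arm. Once each facility has its own indicator, the indicators explain all differences between facilities, including the difference between arms, and nothing is left from which to estimate arm. A small number of clusters is given as the reason for using dummies, but it does not help: facility fixed effects can sit beside a treatment effect only if treatment varies within facilities.

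At stake is whether the coefficient and 95% CI reported for PHQ-9 and GAD-7 mean what the plan says they mean. This is the only between-arm model described for the two outcomes, and the pilot is intended to inform the design of a full trial.

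**Working it through.** **The plan's own figure.** The only design calculation is "95% CI of ± 17% for mentor mothers and ± 11% for adolescent girls", for the loss-to-follow-up rate. At p = 0.5, 1.96 × √(0.25/80) = 11.0% and 1.96 × √(0.25/32) = 17.3%, so it reproduces. The present point does not depend on it.

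**Step 1: identifiability.** Let D_j be the indicator of facility j. Then arm = Σ D_j over the intervention facilities, and setting = Σ D_j over the facilities of one setting type. Both are exact sums of columns already in the model. I checked the design matrix [1, arm, setting, facility dummies less one reference] for 80 girls, with assumed numbers of facilities:

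| Facilities | Columns | Rank | Rank without arm |
|---|---|---|---|
| 4 | 6 | 4 | 4 |
| 8 | 10 | 8 | 8 |
| 16 | 18 | 16 | 16 |

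Arm never adds rank. The result is algebraic and holds for any number of facilities. Girl-level baseline covariates cannot restore it.

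**Step 2: what software would report.** If arm is dropped, there is no estimate. If arm is kept and surplus indicators are dropped, the unadjusted arm coefficient is the mean of one intervention facility minus the mean of one control facility. In one simulated data set with no true effect (8 facilities of 10), the coefficient was 0.81, −2.98, −1.44 or −0.44 depending on which indicator was dropped. The overall arm difference in that data set was −0.75.

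**Step 3: size, if arm is kept.** Assume 80 girls analysed, K equal facilities of m = 80/K, half per arm, total SD 1 and ICC ρ.

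- Variance of a facility mean: V = ρ + (1 − ρ)/m.
- Aliased contrast (one facility against one): 2V. Proper contrast (K/2 against K/2): 4V/K. The ratio is K/2.
- The regression reports 2(1 − ρ)/m for the aliased contrast, where the truth is 2V. This understates the variance by R = 1 + mρ/(1 − ρ).
- Type I error at nominal 5%: P(|t| > t₀.₉₇₅/√R) on 80 − K degrees of freedom.

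At ρ = 0.05 (assumed, since the document gives no ICC):

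| Facilities × girls | R | t₀.₉₇₅/√R | Type I error | Variance ratio K/2 |
|---|---|---|---|---|
| 4 × 20 | 2.05 | 1.99/1.43 = 1.39 | 17% | 2 |
| 8 × 10 | 1.53 | 1.99/1.24 = 1.61 | 11% | 4 |
| 16 × 5 | 1.26 | 2.00/1.12 = 1.78 | 8% | 8 |

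For 8 × 10, the same formula gives 7% at ρ = 0.02 and 17% at ρ = 0.10. With the planned 33% loss and complete cases only (80 × 0.67 = 53.6 girls, 6.7 per facility), the 8-facility figure at ρ = 0.05 is about 9%.

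**Step 4: the other reading.** With one country dummy in place of facility dummies, [1, arm, country, setting] has full rank (4 of 4) and arm is estimable. Variation between facilities within an arm and setting is then left in an ordinary residual, so the interval ignores it.

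**The case against.** **The dummy is singular in the text and may mean country or stratum.** Possible, but less natural: the sentence says it adjusts for clustering and is chosen because clusters are few, and the randomisation section defines clusters as health facilities. On this reading the stated adjustment for clustering is not made, so the sentence still needs correcting.

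**PHQ-9 and GAD-7 are measured three times.** With facility dummies, time and an arm-by-time term, the effect is estimable (rank 10 of 10 for 8 facilities). That is correct, but no repeated-measures model is described, and the stated target is a plain difference in means between arms.

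**This is a pilot that does not set out to detect an effect.** This stands as a limit on the consequence. The analysis section makes implementation outcomes primary, no progression criterion uses a PHQ-9 or GAD-7 effect, and the discussion of minimally important differences draws on within-arm changes that need no cluster dummies. It does not repair a specific model that the article commits to.

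**Detail belongs in an analysis plan.** Nothing is said here to be missing. The objection is to a model the article states.

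**Stronger readings that the documents do not support.** A reader might infer that the plan rules out an ICC. It does not: the between- and within-facility mean squares still give one, and the document promises none. A reader might also infer that a correct analysis must give wider intervals. That depends on the unstated number of facilities. At ICC 0.05 with 8 × 10, and 5 degrees of freedom after arm and setting, the proper half-width is 2.57 × √(4 × 0.145/8) = 0.69 SD. The aliased contrast gives 1.99 × √(2 × 0.95/10) = 0.87 SD.

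**Conclusion.** The point holds. On the natural reading the promised arm difference is not identified, and that rests on algebra alone. On the alternative reading it is identified, but facility clustering goes unadjusted.

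The numerical consequences are conditional. Type I error of about 17%, 11% or 8%, and variance 2, 4 or 8 times that of the proper contrast, assume 4, 8 or 16 equal facilities, 80 girls analysed, ICC 0.05, and software that keeps arm. If arm is dropped, these figures do not apply and there is simply no estimate. They also matter mainly as a sign that the 95% CI would under-cover, since no formal test is planned.

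It would be too strong to say that the pilot's main conclusions fail: its implementation outcomes and progression criteria do not use this model. The correction is still needed, because depression is elsewhere called the primary outcome and no other between-arm analysis of it is described.

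**What to change.** Delete the facility dummies from the PHQ-9 and GAD-7 models and estimate the arm difference in one of two ways:

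- a cluster-level analysis of facility means, or of facility means of covariate-adjusted residuals, with a t reference on cluster-based degrees of freedom; or
- a linear mixed model with a random facility intercept, fixed effects for arm and randomisation strata, and a small-sample degrees-of-freedom correction.

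If a country or stratum dummy was intended, say so and add one of these to account for facilities.

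The cost is a sentence or so in the quantitative analysis section and no new data. The downside is low degrees of freedom. With 4 facilities, arm and setting leave 1 degree of freedom (t = 12.7), and the half-width at ICC 0.05 would be 12.7 × √0.0975 ≈ 4.0 SD, which is uninformative. With 8 or more it is usable but may still be wide, and each further stratum term costs another degree of freedom. Any ICC reported from so few facilities will be imprecise and should be presented that way.

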### Aim and objectives

The aim of the pilot is to refine the Thriving Mamas programme to improve its implementation and impact on the mental health and wellbeing of pregnant adolescent girls and new mothers aged 15–19 years living in Kenya and Mozambique. To achieve this goal, the study has five objectives:Evaluate and understand how local contexts influence stakeholder perceptions of the acceptability, appropriateness, and feasibility of the intervention and its implementation strategies.Explore the impact of the intervention on adolescent mother’s mental health, quality of life, social support, parenting, and health behaviour outcomes.Compare implementation and clinical outcomes in Kenya and Mozambique.Estimate the cost of delivering the intervention.Refine the training materials, intervention content, and procedures for implementation.

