**Health and wellbeing**														
*Depression*^a^	Patient Health Questionnaire (PHQ-9) [9]			X				X					X	
*Anxiety*^a^	Generalised Anxiety Disorder (GAD-7) [7]			X				X					X	
*Quality of life*^a^	WHO Quality of Life short version (WHOQoL-BREF) [26]			X										X

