#### Adolescent girls

A variety of variables will be collected from adolescents by mentor mothers and/or a member of the research team at pre-intervention, meeting 4 and post-intervention to investigate the impact of the intervention.*Depression*: Depression is the primary outcome for our study. The Patient Health Questionnaire (PHQ-9; [26, 27]) is a self-administered screening instrument for common mental disorders. The PHQ-9 is the depression module, which scores each of the 9 DSM-IV criteria as “0” (not at all) to “3” (nearly every day). The PHQ-9 has been validated in Kenya [28] and Mozambique [29].*Anxiety*: The Generalised Anxiety Disorder (GAD-7) measure is a seven-item screening tool for anxiety disorder. Each item scores a symptom of anxiety from “0” (not at all) to “3” (near every day). A GAD-7 score ≥ 10 indicates moderate to severe anxiety. The GAD-7 has been validated in Kenya [30] and Mozambique [31].*Quality of life*: Quality of life will be assessed using the short version of the WHO Quality of Life brief version (WHOQOL-BREF; [32]). The WHOQOL-BREF assesses a respondent’s perceived quality of life across four domains: physical health; psychological; social relationships; and environment. Its 26 items are scored on a five-point Likert scale with higher scores indicating greater agreement. The items are allocated to each domain to provide domain scores with higher scores indicating greater quality of life in a particular domain. The WHOQOL-BREF has been used with adolescents in Kenya [33].*Social support*: The Multidimensional Scale of Perceived Social Support (MSPSS) is a 12-item scale which measures social support from family, friends, and significant others [34]. Each item scores the extent to which the respondent agrees with the statements on a Likert scale with “1” (very strongly disagree) to “7” (very strongly agree). The scale has been validated in adolescents in Ghana [35].*Parenting competency*: The Parenting Sense of Competency Scale is a 17-item scale to measure parents’ perceived parenting abilities [36]. The items are rated on a 6-point Likert response scale from “strongly disagree” to “strongly agree.” Overall parenting competence is derived from a total score where higher scores indicate greater perceived competence. The scale has been used to evaluate parenting competence among mothers of infants aged 2–12 months [37, 38].*Service utilisation*: Antenatal appointment attendance information will be collected from adolescent girls through two questions (i.e. How many antenatal appointments were you scheduled to attend since our last meeting? How many of those appointments did you attend?). Uptake of referrals to community services will be collected from adolescent girls through three questions (i.e. Have you been referred to any community services by your intervention provider? If yes, which services have you been referred to? If yes, have you made contact with these services?).*Health behaviours*: Family planning intentions will be assessed using quantitative questions regarding actual or intended contraception use and intended time to next pregnancy. Actual or intended breastfeeding and infant vaccinations will also be collected through a single question for each variable to determine the impact of the intervention on these behaviours.*Provider competency*- The Mentor mothers’ competency will be assessed using the ENACT tool which was adapted to improve relevance to the study. ENACT tool measures a set of therapeutic competencies required for the effective intervention, including the delivery by the non-specialists [39].

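### The PHQ-9 and GAD-7 regression does not fix the baseline score as a covariate, and leaves its inclusion to an undefined judgement of imbalance

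*Protocol article*

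**What the plan says.** The Quantitative analysis section evaluates PHQ-9 and GAD-7 with "linear regression models that adjust for clustering using a dummy variable (due to the small number of clusters), urban vs rural setting"; the list of adjustments ends with "urban vs rural setting, and any obvious imbalances between treatment arms determined at baseline". It then states: "Coefficients and associated 95% confidence intervals for these outcomes represent differences in means between intervention and control arms". The baseline score is not in this list, and neither is country. Nothing defines which imbalances count as obvious.

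Other places in the article that bear on the model:

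- **Adolescent girls** (under the data collection procedures): measures are taken "at pre-intervention, meeting 4 and post-intervention to investigate the impact of the intervention". Table 1 marks PHQ-9 and GAD-7 at Pre, meeting 4 and meeting 9, so a baseline score is planned for every girl. This section also names depression as the study's primary outcome.
- **Randomisation**: health facilities are the clusters, and the allocation is meant to "ensure the inclusion of an urban and peri-urban site in both the intervention and control groups".
- **Setting**: the Kenyan sites are described as urban and peri-urban; the Mozambican sites are a city and a rural area.
- **Aim and objectives**: the third objective is "Compare implementation and clinical outcomes in Kenya and Mozambique".
- **Data analyses**: implementation outcomes are named as primary, and pilots of this kind are described as not intended to establish a treatment effect.

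**The concern.** The baseline value of the outcome is usually the strongest single predictor of its follow-up value, and here it is already scheduled for collection. Under the stated rule it is used in some realisations of the trial and not in others, according to how far apart the arms happen to lie and who decides that the gap is obvious. Two competent analysts could fit different models to the same data and report different arm differences and intervals.

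These estimates are meant to help plan a full trial, so their precision and reproducibility matter even though no formal test is intended. The setting term adds a smaller problem: the model codes urban against rural, while the stratification is urban against peri-urban. The Kenyan peri-urban site has no defined place in the first coding, and the rural Mozambican area has none in the second.

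**Working it through.** **Plan's own figure.** The article gives no SD, correlation, intracluster correlation, number of facilities or precision for the PHQ-9/GAD-7 model. Its only precision figures concern the loss-to-follow-up rate and do not bear on this point.

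**Inputs.** 80 girls; 40 per arm, taken from the 40 friends or family members, one per intervention girl. With 33% loss, 40 × 0.67 = 26.8, about 27 per arm. Baseline-to-follow-up correlation r: assumed 0.4 to 0.6.

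**Step 1: always adjusting against never adjusting.** For one individual-level baseline covariate and independent observations, the variance of the arm difference is multiplied by 1 − r². The 95% half-width in SD units is 1.96 × √(2/n) × √(1 − r²), with n per arm.

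| r | 1 − r² | width factor √(1 − r²) | half-width, n = 40 | half-width, n = 27 |
|---|---|---|---|---|
| 0 (no adjustment) | 1.00 | 1.00 | 0.44 | 0.53 |
| 0.4 | 0.84 | 0.917 | 0.40 | 0.49 |
| 0.5 | 0.75 | 0.866 | 0.38 | 0.46 |
| 0.6 | 0.64 | 0.80 | 0.35 | 0.43 |

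Over a wider range of r, 0.3 to 0.7, the variance factor runs from 0.91 to 0.51.

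**Step 2: always adjusting against the stated rule.** The rule sometimes does adjust, so Step 1 uses the wrong comparator for the plan as written. A simulation used 40 per arm, no clustering, no true effect and 10,000 runs, and entered baseline only when the arms differed by more than an assumed 0.25 SD. Baseline entered in about 27% of runs.

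| r | SE, rule | SE, always | ratio | mean CI width, rule | mean CI width, always | coverage, rule |
|---|---|---|---|---|---|---|
| 0.5 | 0.202 | 0.194 | 1.04 | 0.859 | 0.773 | 96.4% |
| 0.7 | 0.178 | 0.161 | 1.11 | 0.823 | 0.638 | 97.4% |

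The rule costs about 4% in SE at r = 0.5. The reported interval is wider than it needs to be (0.859/0.773 = 1.11), because runs left unadjusted carry the larger unadjusted standard error; hence coverage above 95%. The simulated rule treats imbalance in either direction alike, so it gives no reason to expect bias.

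**Step 3: what the clustering term does.** Suppose the dummy variable means one indicator per facility. In assumed layouts of 8 and 16 facilities (2 countries × 2 settings × 2 arms, one or two facilities per cell), the indicators alone have rank 8 and 16. Adding country, setting and arm leaves the rank at 8 and 16. Country is then already absorbed, but so is arm, and the arm coefficient cannot be estimated.

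**Step 4: degrees of freedom.** Assume 8 facilities and a cluster-level analysis. Arm and setting leave 8 − 3 = 5 df (t = 2.571). One more cluster-level covariate leaves 4 (2.776, 8% larger), and two more leave 3 (3.182, 24% larger).

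**The case against.** **The estimates are exploratory and the article is condensed.** Data analyses makes implementation outcomes primary, and no progression criterion uses the PHQ-9 or GAD-7 arm difference. This stands and lowers the severity. It does not remove the point: the article does not leave the covariates to another document but states a rule for choosing them, and it promises arm differences with 95% confidence intervals.

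**The rule would catch a marked baseline imbalance.** This stands. Imbalance is judged on baseline rather than outcome data, so the selection is not driven by results. What remains is discretion over what counts as obvious.

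**Extra covariates are costly with few facilities.** This stands for cluster-level covariates (Step 4) and decides how baseline should enter, not whether it should.

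A reader might infer three stronger claims that the documents do not support:

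- *That omitting country leaves between-country variance in the error term.* Each facility lies in one country, so facility indicators would absorb it. The Randomisation section names only urban and peri-urban as strata, and the third objective does not specify the arm-effect model.
- *That the plan's intervals would be 8% to 20% narrower.* Those are the Step 1 width factors: they compare with never adjusting and ignore clustering. Between-facility variance, which the article does not quantify, could dominate.
- *That the estimate is biased.* The check shows mild conservatism only.

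**Conclusion.** The point holds in a narrow form. The baseline score of the same scale is not a fixed covariate, and the rule that may bring it in has no variable list or threshold. The consequence is lost precision and a model that depends on judgement, not a misleading estimate.

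Size depends on the comparator: the Step 1 variance factors apply only against never adjusting, and the loss under the plan's own rule is the smaller one in Step 2. Both rest on assumed correlations, on independence within facilities and, for the rule, on an assumed cut-off; the article supplies none of these. The mismatch between the two setting codings is a real but minor inconsistency. Whether facility indicators make arm inestimable depends on what the single dummy variable means, which the text leaves open. Severity is low to moderate: depression is called the primary outcome in one section, but the analysis is declared exploratory in another.

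**What to change.** For each of PHQ-9 and GAD-7, pre-specify the follow-up score on arm, the individual baseline score of the same scale, and the setting stratum exactly as used to randomise. Reconcile the urban/rural and urban/peri-urban codings so that all four described areas have a defined category.

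Replace the clustering wording with a method under which arm is estimable. One option is a two-stage analysis: regress individual follow-up scores on baseline and stratum without arm, then compare facility-mean residuals between arms. Another is a mixed or similar model with a small-sample correction. A full set of facility indicators should not be used.

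Add country only if it was part of the allocation and is not already absorbed by the clustering terms. Move adjustment for observed imbalances to a labelled sensitivity analysis.

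Cost: a few sentences and no new data. About one degree of freedom is spent. Because that matters at cluster level with few facilities, the baseline score should enter at the individual level and not as a facility mean.

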**Social support**														
*Social support*^a^	Multidimensional Scale of Perceived Social Support (MSPSS) [12]			X										X

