**Parenting competency**														
*Parenting competency*^a^	Parenting Sense of Competence Scale [17]													X

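### Parenting competency is to be analysed as change from baseline but is measured only at the end, and quality of life and social support are given no between-arm estimate although objective 2 asks about impact

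*Protocol article*

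**What the plan says.** Objective 2 of the protocol article (Aim and objectives) is to "Explore the impact of the intervention on adolescent mother’s mental health, quality of life, social support, parenting, and health behaviour outcomes".

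The Quantitative analysis section treats these outcomes in two ways. PHQ-9 and GAD-7 go into linear regression models, whose coefficients with 95% confidence intervals are the differences in means between arms. For the other clinical outcomes the quantity is "Mean differences from baseline to the end of the intervention", which "will be assessed for clinical outcomes (e.g. quality of life, social support, and parenting competency) in each arm". The results are then discussed with local stakeholders to help in settling minimally important differences (MIDs) for the sample size of the full trial.

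Table 1 gives the schedule. WHOQOL-BREF and MSPSS are each marked at the pre-intervention and post-intervention columns. The Parenting Sense of Competence Scale has one mark, in the last (post-intervention) column. None of the three carries the footnote that limits a measure to girls receiving the intervention, so all three are collected in both arms.

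**The concern.** There are two separate problems.

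First, the analysis named for parenting competency needs a baseline score that the schedule does not collect. The analyst will have to depart from the published plan for this outcome, and the plan does not say how.

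Second, a change within one arm is not an estimate of impact. Girls enrol at up to 28 weeks of pregnancy, and the last programme meeting is 10–12 weeks postpartum. Quality of life and perceived support may well shift over that period whatever the arm. Each arm's change combines that shift with any programme effect, and only the contrast between arms separates them. The plan provides the contrast for PHQ-9 and GAD-7 but states none for the other outcomes in objective 2. At stake are the reading of the pilot's impact data and the material put before stakeholders when the full trial is sized.

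**Working it through.** **1. Can the stated change be computed?** The timepoint columns of Table 1 are training pre and post, intervention pre, meetings 1 to 9, and post: 2 + 1 + 9 + 1 = 13.

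| Outcome | Marked at | Change from baseline computable? |
|---|---|---|
| WHOQOL-BREF | intervention pre, post | yes |
| MSPSS | intervention pre, post | yes |
| Parenting Sense of Competence Scale | post only | no |

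Three possible rescues were checked.

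- *A broken table.* The neighbouring rows read cleanly, with marks at both ends. The post-only schedule also looks deliberate, because the article supports the scale by its use in mothers of infants aged 2–12 months, whereas girls enrol while pregnant.
- *The general timing sentence in the Adolescent girls section* (pre-intervention, meeting 4 and post-intervention). It covers an unspecified set of variables and does not fit WHOQOL-BREF or MSPSS either, as neither is scheduled at meeting 4. It does not give the parenting scale a baseline.
- *Multiple imputation.* The baseline is missing for every girl by design, so there are no observed values from which to impute.

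**2. What does change in each arm show?** The plan gives no figure for these outcomes, so there is none to reproduce. Let both arms change by *s* SD with a true programme effect of zero. The plan would then display *s* for the intervention arm and *s* for control. Subtracting gives the right point estimate, 0, but the plan states no interval for it, and one that allows for clustering cannot be rebuilt from the two arm means.

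**3. Precision of the alternatives.** Inputs: 80 girls, taken as 40 per arm (the article expects 40 friends or family members, one per intervention girl), and 33% loss, so 40 × 0.67 = 26.8, or *n* = 27 per arm. Assumptions: equal SD at both times, pre-post correlation ρ of 0.3, 0.5 or 0.7 (the article gives none), and no inflation for clustering. The 95% half-width is 1.96 × SE, in SD units.

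| Quantity | SE | ρ = 0.3 | ρ = 0.5 | ρ = 0.7 |
|---|---|---|---|---|
| Change within one arm | √(2(1−ρ)/n) | 0.45 | 0.38 | 0.29 |
| Between-arm difference in changes | √(4(1−ρ)/n) | 0.63 | 0.53 | 0.41 |
| Between-arm difference, baseline-adjusted | √(2(1−ρ²)/n) | 0.51 | 0.46 | 0.38 |
| Between-arm difference, post only | √(2/n) | 0.53 | 0.53 | 0.53 |

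Example at ρ = 0.5, baseline-adjusted: 1.96 × √(2 × 0.75/27) = 1.96 × 0.236 = 0.46.

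The baseline-adjusted contrast is tighter than subtracting the two changes at every ρ shown. The within-arm change looks the most precise, but it answers a different question.

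**4. How easily could the intervention-arm change be misread alone?** The plan specifies neither a test nor an interval for these changes, so this is an illustration only. Suppose a reader puts a 95% interval on the intervention arm's change, the true effect is zero, and *s* is an assumed shared change. The chance that the interval excludes zero is Φ(s/SE − 1.96) + Φ(−s/SE − 1.96). With SE = √(2 × 0.5/27) = 0.192 at ρ = 0.5:

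| Shared change *s* | ρ = 0.5 | range, ρ = 0.3 to 0.7 |
|---|---|---|
| 0.2 SD | 18% | 14–27% |
| 0.3 SD | 34% | 26–52% |
| 0.5 SD | 74% | 59–92% |

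**The case against.** The strongest defence is that this is a declared descriptive pilot. The Data analyses section names feasibility, acceptability, appropriateness and fidelity as the primary outcomes and says that such pilots are not designed to detect a treatment effect. Objective 2 only explores impact, and none of the progression criteria uses a change or arm difference in these outcomes. The article is also condensed, and a fuller analysis plan may add a between-arm summary. This stands as an argument against significance testing and against a high severity. It does not remove the need for an estimate: the same paragraph already gives a contrast with an interval for PHQ-9 and GAD-7, and the data for the others are collected. Nor does it touch the missing parenting baseline, where the article contradicts its own schedule.

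A reader might go further in four ways that the documents do not support.

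- *That the randomised control is thrown away, or that time change is credited to the programme.* Change is reported in both arms, so a shared shift would show in control too, and no section attributes it to the intervention.
- *That regression to the mean distorts the changes.* Girls are enrolled on gestation and age, with exclusions for inability to consent or take part. They are not selected on any outcome score.
- *That the MIDs will be set equal to the observed changes.* The article says only that the changes help a discussion with stakeholders.
- *That the PHQ-9 model can simply be extended.* It handles clustering with a dummy variable. If that means one indicator per facility, the indicators are collinear with arm, because facilities are what is randomised.

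**Conclusion.** The point holds at moderate severity. The parenting competency part is a plain contradiction between the analysis section and Table 1: one of the three named outcomes cannot be analysed as written, in any girl in either arm. This rests on the schedule alone and needs no assumption.

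The second part is a weakness in the stated choice of analysis. For quality of life and social support, the article states change in each arm and no between-arm estimate, although the objective concerns impact and the data would support a baseline-adjusted contrast. How much this matters depends on how large the shared pregnancy-to-postpartum change is, which the documents do not say; the shifts of 0.2 to 0.5 SD above are assumptions. The half-widths also rest on 27 girls per arm, the assumed correlations and no clustering, so the between-arm figures are lower bounds on the width to expect.

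**What to change.** Reword the Quantitative analysis section as follows.

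- Take parenting competency out of the change-from-baseline sentence. Report it as the between-arm difference at the post-intervention assessment, with a 95% confidence interval.
- For each of the four WHOQOL-BREF domains and for MSPSS, add the between-arm difference at the post-intervention assessment, adjusted for the baseline score, with a 95% confidence interval.
- Use a method suited to few clusters, for example an analysis of facility-level summaries with degrees of freedom based on the number of facilities. Do not include facility indicators that are collinear with arm.
- Keep the change in each arm as description. In the MID discussion, say that it is neither an intervention effect nor the MID itself.
- Label all these contrasts exploratory, without hypothesis tests.

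The cost is wording and a little analysis time; no new data are needed. The drawback is wide intervals. Half-widths of about 0.4 to 0.5 SD before clustering will exclude little, and clustering will widen them by an amount that the article's text does not allow one to calculate. The post-only parenting comparison also cannot correct for a chance difference between arms at baseline, which is a real possibility with few facilities, and the report should say so.
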